#### Rescue backup of controlled ventilation

2.4.4

In both groups, PSV can be switched to protective controlled modes when predefined criteria are met, which include at least one of the following conditions:

Pressure support level above 20 cmH_2_O;PEEP above 15 cmH_2_O;pH < 7.30;PaO_2_/FiO_2_ ≤ 100 mmHg;Strong inspiratory effort which cannot be controlled by sedation;Unstable hemodynamic status (systolic blood pressure below 90 mmHg with vasopressors or systolic blood pressure above 180 mmHg);Active cardiac ischemia;Unconsciousness (RASS < −3 or SAS < 2);Dangerous agitation that cannot be controlled by sedation (RASS > +2 or SAS > 6).

Data will be documented in patients whose mechanical ventilation is switched to controlled modes. The patients will be reassessed at least every 12 h and transited back to PSV as soon as possible according to the abovementioned criteria. The patients will be visited daily until 28 days after randomization. Data will be documented and reported for those patients whose controlled ventilation is not transited back to PSV during the follow-up.

#### Weaning and extubation

2.4.5

The weaning and extubation process follows clinical guidelines recommended by the American Thoracic Society and the American College of Chest Physicians (27).

The attending physicians assess readiness to initiate the weaning process during daily morning rounds. If all the following aspects are satisfied, an SBT will be performed:

Improvement of the cause of intubation and mechanical ventilation;Hemodynamic stability when the dose of norepinephrine is less than 0.1 μg/kg/min or equivalent and lasts for 6 h at stable or reduced doses;No agitation or coma;SpO_2_ higher than 90% with FiO_2_ less than 0.4 and PEEP less than 5 cmH_2_O.

SBT is conducted by respiratory therapists using the low-level PSV with pressure support of 5 cmH_2_O and PEEP of 5 cmH_2_O. The SBT will last at least 30 min, and criteria for failure of SBT include:

RR of greater than 35 breaths/min for more than 5 min;SpO_2_ of less than 90%;Elevated PaCO_2_ and/or pH of less than 7.3;Heart rate (HR) of greater than 140 beats/min or a sustained change in HR of more than 20%;Systolic blood pressure greater than 180 mmHg or less than 90 mmHg;Signs of cardiac ischemia indicated by dynamic ST changes on ICU monitor or electrocardiogram;Abrupt unconsciousness with RASS below −3 or SAS below 2;Signs of anxiety, agitation, or diaphoresis.

Patients with a failure SBT will be mechanically ventilated with PSV following settings and adjustments according to the original grouping.

Extubation will be performed in endotracheal intubated patients who pass the SBT, and mechanical ventilation will be discontinued in patients with tracheostomy. PSV will be restored to maintain the grouping in patients with reintubation or reapplication of mechanical ventilation via tracheostomy within 7 days. The decision to reintubate and restore mechanical ventilation will be at the discretion of the ICU physician team according to the local standard of care. The duration of mechanical ventilation will be added to the total duration.

### Data collection

2.5

An electronic case report form (eCRF) is designed and available online via the SoJump platform (Changsha Ranxing Information Technology Co., Ltd, Hunan, China) (online table). Before the start of the study, clinical research coordinators who have received training in data collection are assigned to each participating ICU.

Data will be anonymous and coded with a three-level structure (Figure 1B). Level 1 represents each enrolled patient, who will be assigned a unique three-digit number. In Level 2, each cluster (ICU) will be assigned a unique two-digit number. In level 3, clusters randomized to the PMI-targeted or the VT/RR-targeted group will be assigned number one or two, respectively. The eCRF will automatically assign a data code to each patient as xxx-xx-x (patient-cluster-group).

#### Data collected at the study entry

2.5.1

At baseline, demographics, comorbidities, diagnosis for ICU admission, recent medical history, reasons for mechanical ventilation, duration of ventilation before enrolment, conditions of gas exchange, and mechanical ventilation settings will be documented, as will the Acute Physiological and Chronic Health Evaluation II (APACHE II) score at the ICU admission.

#### Data collection during daily visits

2.5.2

All patients will be visited daily between 08:00 and 12:00 until successful weaning or separation of mechanical ventilation, death, hospital discharge, or until 28 days after randomization. Successful weaning or separation of mechanical ventilation is defined as extubation without reintubation or death within the next 7 days, whether post-extubation noninvasive ventilation is used or not, or ICU discharge without invasive mechanical ventilation within 7 days, whichever comes first (28).

Data collected include:

Gas exchange: SpO_2_ and arterial blood gas analysis;Hemodynamics: blood pressure, HR, vasoactive agents, and cumulative fluid balance during the last day;Analgesia and sedation: RASS or SAS score, visual analog scale or critical care pain observation tool, the use of analgesics and sedatives;Sequential Organ Failure Assessment (SOFA) score;Switch to controlled ventilation: whether switching to controlled mode during the last 24 h, reasons, and settings;PSV: pressure support level, PEEP, FiO_2_, VT, and RR;Respiratory drive: the negative airway pressure generated during the first 100 ms against an end-expiratory airway occlusion (airway occlusion pressure, P0.1) (29);SBT: whether performing an SBT during the last 24 h, methods, and results;Extubation or discontinuation of mechanical ventilation: whether performed during the last 24 h;Re-intubation or restoration of mechanical ventilation: whether performed during the last 24 h and reasons;Tracheostomy: whether performed during the last 24 h;Self-extubation: whether occurring during the last 24 h;28-day follow-up: duration of mechanical ventilation, length of stay in the ICU and hospital, and death.

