#### Secondary outcomes

2.6.2

Secondary outcomes include:

Duration of mechanical ventilation before enrollment;Total duration of mechanical ventilation;The time before the first SBT, which is defined as the time interval from intubation and mechanical ventilation to the first SBT attempt;Weaning time, which is defined as the time from the first SBT attempt to successful discontinuation of mechanical ventilation (28);Frequency of prolonged weaning, which is defined following WIND classification (28);Frequency of self-extubation, re-intubation, tracheotomy, and mechanical ventilation longer than 21 daysLength of stay in the ICU and hospital;ICU mortality, hospital mortality, and 28-day mortality.

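### The definition of successful separation has no branch for coming off the ventilator through a tracheostomy, so such patients are dated at ICU discharge or not at all by day 28

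*Protocol article*

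**What the plan says.** Section 2.5.2 of the protocol article (Data collection during daily visits) gives the only written definition of success. Its first branch reads "Successful weaning or separation of mechanical ventilation is defined as extubation without reintubation or death within the next 7 days", whether or not noninvasive ventilation follows. Its second branch reads "or ICU discharge without invasive mechanical ventilation within 7 days, whichever comes first". There is no third branch.

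Section 2.4.5 (Weaning and extubation) describes two ways off the ventilator: "Extubation will be performed in endotracheal intubated patients who pass the SBT, and mechanical ventilation will be discontinued in patients with tracheostomy". It then provides for a return to ventilation by either route, referring to "patients with reintubation or reapplication of mechanical ventilation via tracheostomy within 7 days".

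The definition is used in section 2.5.2 itself, where daily visits continue "until successful weaning or separation of mechanical ventilation, death, hospital discharge, or until 28 days after randomization". In section 2.6.2 (Secondary outcomes), one outcome is "Weaning time, which is defined as the time from the first SBT attempt to successful discontinuation of mechanical ventilation". That section also lists the frequency of tracheotomy and of ventilation beyond 21 days. Section 2.6.1 says that ventilator-free days (VFDs) will be calculated by cited recommendations and does not refer to section 2.5.2.

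**The concern.** The protocol expects tracheostomised patients. It counts tracheotomy as an outcome, records it daily and has a rule for reconnecting these patients. Yet the definition that decides when a patient is liberated covers them only once they leave the ICU. Until then, a patient breathing without the ventilator through a tracheostomy meets neither branch.

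For these patients the recorded date then reflects when the ICU discharges them, not when ventilation stopped. They are likely to be among the longest-ventilated patients. Tracheostomy and discharge practice may differ between ICUs. Section 2.2 matches pairs on bed number and ventilated-patient volume, not on these practices, and the care teams and data collectors are unblinded. Sites may also settle the gap differently, some dating disconnection and others discharge.

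**Working it through.** No stated figure in the plan is in dispute, so the check sets the sections side by side and then works through one example patient.

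**Step 1. Can extubation be read to include tracheostomy disconnection?** Section 2.4.5 applies extubation to endotracheally intubated patients and uses a separate verb for patients with a tracheostomy. The data list in section 2.5.2 also names two events: "Extubation or discontinuation of mechanical ventilation: whether performed during the last 24 h". The protocol's own usage therefore keeps them apart. Reading the word loosely as removal of the tracheostomy tube would not help, because a patient can be off the ventilator with the tube still in place.

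**Step 2. Does the second branch cover the patient?** Only from ICU discharge. Before that, the patient is unclassified.

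**Step 3. Which outcomes use the definition?**

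| Item | Link to the section 2.5.2 definition |
|---|---|
| End of daily visits (2.5.2) | Direct: same section, same term |
| Weaning time (2.6.2) | Ends at successful discontinuation, which has no definition of its own; cites the same source (28) as section 2.5.2 |
| Prolonged weaning (2.6.2) | Delegated to the WIND classification (28); link not stated |
| VFDs (2.6.1) | Delegated to references 30 and 31; link not stated |

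**Step 4. Example patient.** The days are assumed and are not in the documents. Days are counted from enrollment. The patient is disconnected through a tracheostomy on day 12, is never reconnected and survives.

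- By disconnection, separation is on day 12.
- By the literal definition, with ICU discharge on day 22, separation is on day 22. The delay is 22 − 12 = 10 days. Weaning time is lengthened by the same 10 days whatever the day of the first SBT, because the start point is common to both readings.
- By the literal definition, if the patient is still in the ICU on day 28, there is no separation within follow-up and weaning time has no end date.

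**Step 5. The same patient's VFDs, only if the section 2.5.2 date were used for them.** By disconnection, 28 − 12 = 16. By ICU discharge on day 22, 28 − 22 = 6. Still in the ICU on day 28, 0. This shows how far one patient's score depends on the choice of date; it does not estimate a trial-level effect.

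**Step 6. Can a trial-level effect be computed?** No. It would need the share of patients disconnected through a tracheostomy, their ICU stay after disconnection, and the difference in both between arms. The documents give none of these. If share and delay were equal in the two arms, weaning times would lengthen in both and the difference between arms would change little or not at all.

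**The case against.** The strongest reply is that this is shorthand in one sentence. The sentence sits under data collection and its express job is to say when visits stop. If it fails to stop them for a tracheostomised patient, the result is more data, not less. Weaning time ends at discontinuation, the very term that section 2.4.5 uses for tracheostomy, so a sensible analyst would date it to disconnection. The definition cites a source that may contain a tracheostomy rule, a training and operational manual is planned, and an article may leave detail to fuller documents.

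Part of this stands. The procedures and the data list treat the two routes in parallel, and the dates needed are recorded, so the omission is probably unintended and can be repaired without new data. But the article does not leave the definition open. It states a closed rule, and that rule does not fit a route the protocol itself provides. The wording of weaning time does not close the gap either: it requires the discontinuation to be successful, and success is defined only in section 2.5.2.

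A reader might go further and infer that the primary outcome is biased, or that these patients can never count as separated. The documents do not support either inference. VFDs are referred to other sources and not to this definition. A patient who later leaves the ICU without invasive ventilation does count, from that day.

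**Conclusion.** The point holds as an error in a stated rule. The definition omits discontinuation through a tracheostomy, and followed literally it dates separation at ICU discharge, or records none if the patient is still in the ICU at day 28. The end of daily visits is affected directly. The end date of weaning time is affected because no other definition of success is written.

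For VFDs and prolonged weaning, the finding is only that the protocol does not say whether this date is used. It is tempting to set an assumed imbalance in tracheostomy use against the one-day target difference in section 2.9.1, but any such figure would rest wholly on the assumption. The 10-day delay in the example likewise depends on the assumed days.

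This is a correction to make before outcomes are dated. It is not a demonstrated threat to the primary result.

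**What to change.** Add a third branch to the definition in section 2.5.2. For patients with a tracheostomy, success is discontinuation of invasive ventilation with neither its reapplication via the tracheostomy nor death in the next 7 days, dated to the day of disconnection whether or not the patient leaves the ICU. Use that date as the end of weaning time. State in sections 2.6.1 and 2.6.2 that the same liberation date feeds VFDs and the prolonged-weaning classification.

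The cost is one sentence in the definition, the statement of which date feeds each outcome, and matching eCRF guidance. Discontinuation, restoration of ventilation and tracheostomy are already recorded daily, and the 7-day window already exists. No extra patients are needed. The change concerns outcome dating only and leaves clinical care untouched.

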### Outcome measures

2.6

#### Primary outcome

2.6.1

The primary outcome is the ventilator-free days (VFDs) at day 28 after enrollment. The calculation of VFDs will follow the standard recommendations (30, 31).

#### Secondary outcomes

2.6.2

Secondary outcomes include:

Duration of mechanical ventilation before enrollment;Total duration of mechanical ventilation;The time before the first SBT, which is defined as the time interval from intubation and mechanical ventilation to the first SBT attempt;Weaning time, which is defined as the time from the first SBT attempt to successful discontinuation of mechanical ventilation (28);Frequency of prolonged weaning, which is defined following WIND classification (28);Frequency of self-extubation, re-intubation, tracheotomy, and mechanical ventilation longer than 21 daysLength of stay in the ICU and hospital;ICU mortality, hospital mortality, and 28-day mortality.

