#### Exclusion criteria

2.3.2

Age younger than 18 years old;Initiation of PSV before ICU admission;Duration of mechanical ventilation longer than 7 days before enrollment;History of neuromuscular diseases;Clinical suspicion of increased intracranial pressure;Presentation with pneumothorax and/or bronchopleural fistula;Extracorporeal support;Moribund conditions;Refusal by the ICU physicians or the patient.

The patients will be enrolled only once during the same hospitalization. Written informed consent will be obtained from the patient or their legal representative.

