#### Statistical analysis plan

2.9.2

All statistical analyses will be conducted in accordance with the intention-to-treat principle. That is, all randomized patients will be analyzed in the groups to which they were originally allocated. Researchers performing statistical analysis will be blinded to the cluster grouping.

Categorical variables will be presented as numbers and percentages and compared using the chi-squared test or Fisher’s exact test. For continuous variables, normal distribution will be checked by Kolmogorov–Smirnov Test, and presented as mean and standard deviation or median and interquartile range, as appropriate. Comparison of continuous variables will be performed by Student’s *t*-test for normally distributed variables and the Mann–Whitney U test for non-normally distributed variables.

Time-to-event variables will be analyzed using survival analysis, and the difference between groups will be assessed with the log-rank test.

The patients will be stratified *a priori* into subgroups with:

high versus intermediate and low respiratory drive according to the P0.1 criteria reported by a previous study (29);diagnosis of acute respiratory distress syndrome (ARDS) versus non-ARDS according to the Global definition (35);long versus short duration of controlled ventilation before enrollment according to the median obtained in all enrolled patients.

Statistical analyses will be performed using MedCalc (2022 MedCalc Software Ltd., Belgium). A *p* value of less than 0.05 is considered statistically significant.

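### Ventilation time before enrolment is listed as a secondary outcome, and time to first SBT (and probably total duration) is counted from intubation rather than enrolment

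*Protocol article*

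**What the plan says.** Section 2.6.2 opens its list of secondary outcomes with "Duration of mechanical ventilation before enrollment". The next item is "Total duration of mechanical ventilation", with no start point given. Time before the first SBT is "the time interval from intubation and mechanical ventilation to the first SBT attempt". Weaning time is "defined as the time from the first SBT attempt to successful discontinuation of mechanical ventilation". A later item counts patients ventilated for more than 21 days, again without a start point.

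Elsewhere the pre-enrolment period is treated as a patient characteristic:

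- Section 2.5.1, on data at study entry, says that "duration of ventilation before enrolment, conditions of gas exchange, and mechanical ventilation settings will be documented".
- Section 2.3.2 excludes patients on the criterion "Duration of mechanical ventilation longer than 7 days before enrollment".
- Section 2.9.2 uses the length of controlled ventilation before enrolment as a subgroup factor, split at the median.

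For analysis, section 2.9.2 compares continuous variables between groups by t-test or Mann–Whitney U test, with significance at p below 0.05, and makes no exception for the pre-enrolment item. It adds: "Time-to-event variables will be analyzed using survival analysis, and the difference between groups will be assessed with the log-rank test". It does not say which outcomes count as time-to-event variables.

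**The concern.** An outcome should be able to respond to what is being compared. Section 2.4 limits the contrast between arms to how pressure support is adjusted during pressure support ventilation, and patients enter within 24 h of starting that mode. Time on the ventilator before entry is essentially settled by then. Followed as written, the plan would test a baseline quantity at the 5% level and report it among the trial's results.

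This is more than a label, because pre-enrolment time may well differ between arms for reasons unrelated to the strategy's effect. There are only 16 ICUs, matched on beds and volume of ventilated patients rather than on weaning or mode-transition habits. Allocation is unblinded. Staff are trained separately by arm, in courses that cover initiation of pressure support, before any patient is enrolled (sections 2.2 and 2.7). Enrolment is triggered by the start of pressure support, so an ICU's habits on when to make that switch help to fix the pre-enrolment time of its patients. Any outcome counted from intubation inherits that difference, and a reader could take it for a treatment effect.

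**Working it through.** **The plan's own figures.** The article gives no figure for these secondary outcomes. Its only calculation concerns ventilator-free days, and it reproduces:

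- Per arm: 2 × (1.960 + 0.842)² × 3.3² / 1² = 171, so 342 in all.
- Cluster step: 342 × [1 + (342/16 − 1) × 0.03] = 342 × 1.611 = 551.
- Inflation for immeasurable PMI: 551 / 0.85 = 648.

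These figures rest on an outcome counted from enrolment (section 2.6.1), so this point does not change them.

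**Which outcomes contain pre-enrolment time.**

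| Outcome | Clock starts | Pre-enrolment time included? |
|---|---|---|
| Ventilation before enrolment | start of ventilation | it is nothing else |
| Time before first SBT | intubation (stated) | yes, up to 7 days |
| Total duration | not stated; intubation is the natural reading | probably, up to 7 days |
| Ventilation beyond 21 days | not stated; same natural reading | probably, up to 7 days |
| Weaning time | first SBT (stated) | no, unless an SBT preceded enrolment |
| Ventilator-free days (primary) | enrolment (stated) | no |

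**Effect on the comparison of means.** Write P for days ventilated before enrolment (0 to 7 by the exclusion criterion) and T for days from enrolment to the event. An intubation-based duration is P + T.

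- Difference in means: Δ(P + T) = ΔP + ΔT. If P is balanced, ΔP = 0 and the expected difference is still ΔT. If it is not, ΔP is added in full. As an illustration only, take an assumed true reduction of 1 day (ΔT = −1) and an assumed imbalance of 0.5 day in either direction. The observed difference is then −1 + 0.5 = −0.5 or −1 − 0.5 = −1.5 days.
- Variance: Var(P + T) = Var(P) + Var(T) + 2 Cov(P, T). This exceeds Var(T) unless the covariance is below −Var(P)/2, that is, unless longer prior ventilation goes with clearly shorter later ventilation. Precision is therefore expected to fall. The article gives neither variance nor the covariance, so the loss cannot be computed.

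**Effect on the 21-day outcome.** Under the intubation reading, a patient enrolled after 7 days of ventilation reaches the threshold 21 − 7 = 14 days after enrolment, while a patient enrolled at the start of ventilation needs the full 21. The same event then asks for between 14 and 21 days under the allocated strategy, depending on a baseline characteristic.

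**The case against.** The best defence is that comparing pre-enrolment time is informative. ICUs are randomized first, their staff are trained by arm, and up to 24 h of pressure support may precede enrolment. Allocation could thus shift pre-enrolment time, and a reader who infers that it cannot be affected at all goes too far. This stands, but it supports showing the variable at baseline as a check on transition and recruitment. It does not make it an outcome of the adjustment strategy.

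It is also fair to say that the quantity is already collected at entry, that a related quantity is already a subgroup factor, and that total duration from intubation is a legitimate description of the illness. The fix below keeps intubation-based times for that purpose.

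Three stronger readings are tempting, and the article does not support them:

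- **All duration outcomes are compromised.** The table above shows otherwise. The intubation origin is explicit only for time to first SBT; for total duration and the 21-day outcome it is an inference.
- **A definite loss of power.** Any such figure must borrow the 3.3-day SD and one-day effect of section 2.9.1, which belong to ventilator-free days. It must also assume a spread for pre-enrolment time and its correlation with later duration. No secondary outcome was powered.
- **The log-rank test cannot accommodate death.** A log-rank test that censors deaths compares cause-specific hazards, which is a valid comparison. Section 2.9.2 does not say which outcomes receive this test or from what origin, and such detail is commonly left to a full analysis plan.

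**Conclusion.** The point holds, limited to secondary outcomes. A quantity fixed before entry, and recorded as baseline by the article itself, is misplaced among the outcomes. Time to first SBT explicitly includes up to 7 days that precede enrolment. Total duration and the 21-day outcome do so on their natural reading, and this part rests on an inference about an unstated start point.

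The consequence is twofold. An imbalance in mean pre-enrolment time enters the mean durations one for one, and precision is expected to fall by an unknown amount. With balance, the expected difference in mean days is unchanged. Whether an imbalance will occur cannot be known in advance; 16 unblinded ICUs with arm-specific training before enrolment make it plausible. The change should be made before analysis.

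**What to change.** 1. Section 2.6.2: remove ventilation time before enrolment from the outcomes. Report it by arm with the baseline data, and read any difference as information on balance, transition to pressure support and recruitment.
2. Section 2.6.2: for the comparison between groups, define time to first SBT, total duration and the prolonged-ventilation outcome from enrolment. A 21-day threshold counted this way still falls within the 28-day follow-up. Say how a patient whose first SBT preceded enrolment is counted, since the eligibility criteria do not exclude this. Keep intubation-based times as descriptive.
3. Section 2.9.2: name pre-enrolment ventilation time as an adjustment covariate for these outcomes. The listed t-test, Mann–Whitney and log-rank comparisons are unadjusted, so a regression model has to be added.
4. Optional: show cumulative incidence of first SBT and of successful weaning, with death as a competing event, beside any log-rank comparison.

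The cost is wording in two sections and a modest addition to the analysis. Sections 2.5.1 and 2.5.2 already collect prior ventilation, SBTs, extubation and death. The primary outcome and the sample size do not change.
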